## Abstract

Non‐vitamin K antagonists oral anticoagulants (NOACs) have recently challenged vitamin‐K antagonists (VKAs) for stroke and systemic embolism prophylaxis in patients with non‐valvular atrial fibrillation (NVAF). Nevertheless, little information is available in routine clinical practice for France. The aim of this study is to describe the effectiveness and safety of apixaban, rivaroxaban, dabigatran or VKAs in routine clinical practice in adult NVAF patients for the prevention of stroke and systemic embolism in France. The NAXOS study is a nationwide observational retrospective cohort generated from the French national healthcare insurance database (SNIIRAM—a comprehensive in‐ and outpatient healthcare consumption database), consisting of eight distinct sub‐cohorts of anticoagulant‐naive or anticoagulant‐experienced patients diagnosed with NVAF, newly initiated with either NOACs (dabigatran, rivaroxaban or apixaban) or VKAs. Patients will be included if initiating a new anticoagulant treatment for AF during the study period from 1 January 2014 to 31 December 2016. Primary effectiveness outcome will be the incidence of stroke or systemic thromboembolic events; primary safety outcome will be the incidence of major bleeding during the exposure period. The NAXOS study will provide routine clinical practice data on the effectiveness and safety profiles of apixaban vs other NOACs and VKAs in the prevention of stroke and systemic embolism in adult patients with NVAF in clinical practice conditions in France.

AbbreviationsAFatrial fibrillationCMAContinuous Measure of Medication AcquisitionCNILFrench data protection commission, “*Commission Nationale Informatique et Libertés*”ICDInternational Classification of DiseasesIDSInstitute of health data, “*Institut des Données de Santé*”LTDlong‐term disease, “*Affection Longue Durée*”NOACsnon‐vitamin K antagonist oral anticoagulantsNVAFnon‐valvular atrial fibrillationPMSIFrench Hospital Discharge databaseSNIIRAMFrench National Health Insurance Information SystemVKAsvitamin‐K antagonists

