## INTRODUCTION

1

Atrial fibrillation (AF) can lead to significant mortality, morbidity, and cost.^1^, ^2^ Long‐term prophylaxis with anticoagulation therapy is recommended to prevent stroke and systemic embolization in patients with AF presenting an independent risk factor for stroke.^3^ Four non vitamin‐K antagonists oral anticoagulants (NOACs) are currently available: the direct factor Xa inhibitors (rivaroxaban, apixaban, and edoxaban) and the direct factor IIa inhibitor (dabigatran). These four NOACs have demonstrated, in randomized clinical trials, a consistent favorable risk‐benefit profile across a wide range of patients with reductions in stroke or systemic embolism, intracranial hemorrhage, and mortality but increased gastrointestinal bleeds when compared with warfarin.^4^, ^5^, ^6^, ^7^, ^8^

Clinical practice data regarding routine use of the different NOACs largely mirrors the results of clinical trials.^9^, ^10^, ^11^, ^12^, ^13^ In addition, a recent study using the French medico‐administrative databases (SNIIRAM and PMSI), including patients with NVAF who initiated dabigatran or rivaroxaban was previously reported but did not include data on apixaban.^14^ The French Health Authority (HAS) Transparency Commission granted positive appraisal in June 2013 to the reimbursement of apixaban in the indication of stroke prevention and systemic embolism in patients with NVAF, with one or more risk factors, such as prior stroke or transient ischemic attack, age ≥ 75 years, hypertension, diabetes mellitus, and symptomatic heart failure (NYHA ≥ class II). However, while recommending the reimbursement of apixaban in this indication, HAS requested clinical practice data documenting the therapeutic benefit of apixaban under actual conditions of use, compared with the standard oral anticoagulant treatment recommended in France (vitamin‐K antagonists, dabigatran, and rivaroxaban). Indeed, limited clinical practice data are available on the characteristics, clinical management, and outcomes of patients treated with apixaban in France. The availability of warfarin and three NOACs in France allows opportunities for comparative analyses, particularly on the effectiveness and the safety of these drugs when used outside the controlled setting of clinical trials. Nevertheless, as edoxaban was only recently introduced to the market, and not yet available in France, this analysis will only focus on VKAs, dabigatran, rivaroxaban, and apixaban.

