**Figure 1 clc23231-fig-0001:**
[figure not shown]
Study design. AC, anticoagulant; AF, atrial fibrillation; NVAF, non‐valvular atrial fibrillation

Using the French National Health Insurance System (SNIIRAM) database, patients were identified and included in the study if they initiated a new anticoagulant treatment from 1 January 2014 to 31 December 31 2016. The study will be led by a project team, a coordinating center and a scientific board which is detailed in the Supporting Information Appendix 1.

Patients will be followed from the date of their first OAC prescription until the end of follow‐up, which is defined by the occurrence of a following event, whichever comes first:
*Switch to another anticoagulant treatment*: defined as dispensation of another anticoagulant molecule recorded after initiation of the studied anticoagulant treatment. Date of switch (and end of follow‐up) will be the date of the first dispensation of the other anticoagulant molecule.
*Discontinuation*: a patient who remains more than 30 days after the coverage by the last dispensation of studied anticoagulant treatment without refilling it will be considered as stopping this treatment. If a hospitalization occurs within this period, the length of the hospital stay will be deducted from the number of days without refilling of the treatment. For patients treated with VKAs, International Normalized Ratio testing realized during a hospitalization will be counted as a VKA dispensation. International Normalized Ratio testing will be used as a proxy of a VKA prescription only to extend VKA treatment exposure, but it will not be used as an index date. OACs drug coverages will be derived based on the recommended dosage, and the coverage of VKA treatment exposure will be defined as 35 days (ie, the median coverage time in days of VKA treatments, based on prior assessment on claims database). The median number of coverage days will also be calculated in the VKA patient population after data extraction.
*Last patient's health record*: defined by the last care (ie, consultations, dispensations, medical procedures…) recorded in the database before a period of 6 months without any reimbursed care. This includes situations like emigration and geriatric homes entry.
*Patient's death*.
*End of study period*.

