**Figure 2 clc23231-fig-0002:**
[figure not shown]
Global flow chart of the study population. AC, anticoagulant; AF, atrial fibrillation; VKA, vitamin‐K antagonist

Anticoagulant‐naive patients will be defined as patients with no dispensation of anticoagulant treatment during the 24 months before the index date, and anticoagulant‐experienced patients corresponding to the others. Patients in the experienced group will only be included at their first entry. Therefore, all patients aged ≥18 years and covered by the French national health insurance general scheme, with at least one reimbursement for OAC treatments (VKAs, apixaban, rivaroxaban, or dabigatran) between January 2014 and December 2016, and without use of the same OAC in the 24 months before the index date (ie, date of the first dispensation) will be included. Only the first dispensation meeting this criterion determined the index date, that is, a patient could be included only once in the study.

Then, patients selected were allocated to four distinct sub‐cohorts of OAC‐naive patients (ie, with no dispensation of any OAC during the 24 months before the index date), receiving either VKAs, apixaban, rivaroxaban, or dabigatran during the study period. Anticoagulant‐experienced patients corresponded to the others.

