Secondary outcomes:Risk of occurrence of a composite morbidity criterion: unadjusted incidence rate in each sub‐cohort, composite morbidity criterion being defined by stroke, systemic thromboembolic events, and/or major bleeding, whichever occurs first.Risk of all‐cause mortality: unadjusted incidence rate of all‐cause death in each sub‐cohort.Major characteristics of patients and comorbidities, which are summarized in Table 2.Treatment patterns at anticoagulant initiation: Type of the prescriber initiating the anticoagulant treatment (general practitioners, office‐based cardiologists, hospital‐based physicians, and others), dispensed dosages, number of dispensed packaging at anticoagulant initiation, co‐prescription of dispensed treatments (other anticoagulants, antiplatelet agents, nonsteroidal anti‐inflammatory drugs, serotonin‐specific reuptake inhibitors, strong inhibitors of both CYP3A4 and P‐gp, HIV protease inhibitors, anticonvulsants, strong inducer of hepatic enzymes, and antiarrhythmic drugs) in each sub‐cohort.Treatment patterns over time:Adherence to treatment: Continuous Measure of Medication Acquisition version 7 (CMA 7).^16^
Persistence: number and percentage of persistent and non‐persistent patients over the 6 months and the 12 months after index date, time‐to‐event of persistence, median duration of persistence, number and percentage of non‐persistent patients with other anticoagulant therapy administered after discontinuation, during the gap, the number and percentage of persistent patients who had concomitant dispensings of other anticoagulant treatment over the exposure period of the studied anticoagulant, the number and percentage of non‐persistent patients who switched from studied anticoagulant treatment and re‐exposed after the switch during a 1‐year period, in each sub‐cohort.
Healthcare resources utilization description: use of medical visits, nurse acts, drugs packages delivered, biology acts, medical procedures, hospital stays, and sick leaves will be reported as:The number and percentage of patients with at least one reimbursement of a such healthcare resource use during the follow‐up period.The mean, SD, median, percentiles 10 and 90 of the number of care, only in patients with at least one reimbursement of the healthcare during the follow‐up period.

**Table 2 clc23231-tbl-0002:** Major patients characteristics and comorbidities evaluated for each anticoagulant

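### Re-exposure after a switch is a listed outcome, but follow-up ends on the day of the switch; if later dispensings are read up to the end of 2016, a crude percentage is too low

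*Protocol article*

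**What the plan says.** Section 3.1 (Data source and study population) sets one follow-up rule for every patient. Follow-up runs from the first prescription to an end "which is defined by the occurrence of a following event, whichever comes first". The listed events are switch, discontinuation, last health record, death and "End of study period". For a switch the rule is explicit: "Date of switch (and end of follow‐up) will be the date of the first dispensation of the other anticoagulant molecule".

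Section 3.2 (Study outcomes), under persistence, asks in each sub-cohort for the number and percentage of non-persistent "patients who switched from studied anticoagulant treatment and re‐exposed after the switch during a 1‐year period". It does not say whether the year starts at the index date or at the switch, and it exempts nothing from the follow-up rule.

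The only dates for the study period are in the Abstract, which has patients included if they start treatment "during the study period from 1 January 2014 to 31 December 2016". The same dates therefore define both the inclusion window and the study period. No data-extraction date is given. Section 3.1.2 (Study population) adds that "a patient could be included only once in the study".

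**The concern.** A return to the studied drug after a switch always comes after the switch, and the switch is the end of follow-up. A programmer who applies section 3.1 literally has no time at risk in which to count the event. One who ignores the rule and reads later dispensings will produce a figure, but patients who switched near the end of the records have not had a year in which to return. If they stay in the denominator of a simple percentage, the result is too low.

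What is at stake is one descriptive item in eight sub-cohorts. Section 3.4.2 has treatment patterns tabulated by drug, so readers will see these percentages side by side. The primary effectiveness and safety estimates do not depend on them.

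**Working it through.** The article states no re-exposure figure, so there is nothing of its own to reproduce. The check has two steps.

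**Step 1: the rules side by side.**
- Follow-up ends on the day of the first dispensation of the other drug (section 3.1).
- The outcome requires a dispensation of the studied drug after that day (section 3.2).
- A second inclusion cannot recover the time after the switch, because each patient enters once (section 3.1.2).

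Follow-up after the switch is 0 days, so no re-exposure can be observed, whichever date the one-year window starts from.

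**Step 2: the rule waived, records ending on 31 December 2016.**

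Input from the article: an inclusion window of T = 3 years (1 January 2014 to 31 December 2016, 1,096 days).

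Assumptions, none of them in the article:
- records stop at T;
- the one-year window starts at the switch;
- entry is uniform over the three years;
- time to switch is exponential with mean m years;
- true re-exposure within the year is either spread evenly or front-loaded (mean about 3 months).

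With uniform entry, the density of switches at calendar time s is proportional to f(s) = 1 − exp(−s/m) for s < 3. The share of observed switchers with a full year ahead of them is

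∫₀² f(s) ds / ∫₀³ f(s) ds = [2 − m(1 − e^(−2/m))] / [3 − m(1 − e^(−3/m))].

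For m = 1: (2 − 0.8647) / (3 − 0.9502) = 1.1353 / 2.0498 = 55%.

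With re-exposure spread evenly over the year, the share captured is

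[∫₀² f(s) ds + ∫₂³ (3 − s) f(s) ds] / ∫₀³ f(s) ds.

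For m = 1: (1.1353 + 0.4502) / 2.0498 = 77%.

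Uniform entry, by mean time to switch:

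| Mean time to switch | Full year available | Captured, evenly spread | Captured, front-loaded |
|---|---|---|---|
| 3 months | 64% | 82% | 92% |
| 6 months | 60% | 80% | 91% |
| 12 months | 55% | 77% | 89% |
| 24 months | 51% | 75% | 88% |

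Over these cases the crude percentage recovers about 75-92% of the true value. A true 10% would be reported as about 7.5-9.2%.

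Other entry patterns, by simulation with means of 3 to 12 months:
- early-weighted entry (linearly falling): 86-98% captured;
- late-weighted entry (linearly or quadratically rising): 55-85% captured.

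**If the year starts at the index date,** the shortfall is smaller. With uniform entry, patients included in 2014-2015 outnumber those included in 2016 by two to one, and each is at least as likely to have an observed switch. At least 2/3 = 67% of observed switchers then have a complete window, against 51-64% above. Step 1 is unchanged.

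**The case against.** The strongest reply is that the persistence items carry their own windows. Some run 6 or 12 months from the index date, one looks at therapy after discontinuation, and one at the exposure period. Only the healthcare-use items are tied to follow-up. On that reading a specific window overrides the general rule, and the claims database would hold the later dispensings. This is a fair account of what was probably meant, and it shows that the obstacle is the rule and not the data source. But section 3.1 states no exception, so the two sections still need to be reconciled.

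A second reply is that this is a condensed article, and that the denominator and censoring of one descriptive item belong in a fuller document. That covers missing detail. It does not cover a stated follow-up rule that excludes a stated outcome. The article also already handles unequal follow-up by cumulative incidence, for the primary outcomes (section 3.4.1) and for time to discontinuation (section 3.4.2), whereas this item is given only as a number and percentage.

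A reader might infer more than the article supports:
- **That all data end on 31 December 2016.** That date closes the study period, but no extraction date is given. If later records are read, the truncation shrinks or disappears.
- **That the shortfall can be assigned to a particular drug, or that differences between drugs would arise from calendar time alone.** The article gives no uptake by drug. The Introduction says only that the French health authority "granted positive appraisal in June 2013 to the reimbursement of apixaban". Later entry makes the shortfall larger, but which sub-cohort entered later is not stated.
- **That a planned comparison is distorted.** Section 2 limits comparisons to baseline characteristics, clinical outcomes and healthcare use, and this item is not among them.
- **That counting deaths as not re-exposed is an error.** A cumulative incidence with death as competing event does the same, and it is a legitimate quantity.

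**Conclusion.** The contradiction stands on the article's own text: a listed outcome lies wholly after the defined end of follow-up, and no exception is stated. The downward bias is conditional. It arises if the rule is waived, records stop at the end of 2016, and patients without a full year stay in a crude percentage. Under assumed uniform entry the percentage then recovers very roughly 75-92% of true one-year re-exposure, and less with later-weighted entry. The entry pattern, time to switch and timing of return are all assumed, so these figures show the order of size and are not an estimate for this study. The item is secondary and descriptive. It should be corrected because the correction is cheap and the tabulated figures could otherwise be wrong.

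**What to change.** 1. In section 3.1, state that end of follow-up at switch does not apply to re-exposure after a switch.
2. In section 3.2, state whether the one-year window starts at the index date or at the switch, and give the date on which the data end.
3. Then choose one of two summaries:
   - among patients who switched, the cumulative incidence of re-exposure at 365 days, censored at last health record or end of data, with death as competing event; or
   - a percentage limited to patients whose full one-year window lies before the end of data.
4. State the denominator. The item is worded for non-persistent patients who switched, so a percentage of switchers and a percentage of all non-persistent patients need to be told apart.

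The cost is a few sentences and a small programming change. The restricted percentage counts fewer switchers; the cumulative incidence keeps them all.

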### Ethics and confidentiality of study data

3.3

This study does not require review and approval by ethics committees or informed consent. The confidentiality of records that could identify patients within the database will be protected, respecting the privacy and confidentiality rules in accordance with the applicable regulatory requirements. This database analysis will use anonymous patient's data.

### Statistical analyses

3.4

#### Primary effectiveness and safety outcomes

3.4.1

For primary effectiveness outcome, estimates by anticoagulant treatment and for both populations (anticoagulant‐naive and anticoagulant‐experienced patients) of:The number and percentage of patients presenting at least a stroke and/or a systemic embolic event during the 12 months after index date, and during the overall follow‐up period. This description will be also conducted by diagnoses sub‐division presented in Table 1.The unadjusted incidence rate: number of first event of stroke and/or systemic embolism by 100 person‐years and during the overall follow‐up period will be estimated by anticoagulant treatment. Person‐years are defined with the sum of follow‐up durations of the at‐risk population. The corresponding two‐sided 95% CI will also be represented using Poisson distribution.The time‐to‐event of first occurrence of stroke and/or systemic thromboembolism will be estimated and plotted using cumulative incidence function (the cumulative probability of failure from a specific cause over time) accounting for differences in follow‐up time and the competing risk of mortality (if mortality is greater than 10%). In the presence of competing risks of mortality, informative censoring of the observation time at death will be used, as mortality will be considered a competing risk for observing stroke and systemic thromboembolic events since patients who die before an event is observed cannot go on to have an event. In the absence of competing risks, the differences in follow‐up time will be accounted for through non‐informative censoring of the observation time at the end of follow‐up for each patient. Overall, the causes of censoring of each treatment group will be reported once the results will become available. Cumulative incidence curves will present the event risk over time (within first 12 months) for each newly initiated anticoagulant treatment while accounting for the competing risk of mortality (if needed) and differences in follow‐up time.Median duration to occurrence of first event of stroke and/or systemic thromboembolism: median duration (in days) between the index date and the date of the first studied event will be computed for patients with the event.

For primary safety endpoint, estimates by anticoagulant treatment and for both populations (anticoagulant‐naive and anticoagulant‐experienced patients) will be addressed by using the same methods as described for the primary effectiveness endpoint.

In order to account for confounding in the comparative analyses, several methods will be performed to compare groups of patients with the similar characteristics including: adjustment on propensity score (estimation of the average treatment effect in the entire population if the treatment might be offered to every member of the population, ATE), matching on propensity score (estimation of the average treatment effect of matched subjects who ultimately received the treatment, ATT), and two other comparative approaches as sensitivity analyses (using high dimensional propensity scores, and adjustment on confounders).

The main method will consist in propensity score adjustment to compare groups of patients with the same characteristics. The propensity score is the probability of treatment assignment conditional on observed baseline characteristics. Propensity score is used when selection bias due to non‐random treatment assignment is likely, because of observational data. Three different propensity scores will be performed according to the comparison (apixaban vs dabigatran, apixaban vs rivaroxaban or apixaban vs VKAs). The propensity score conventional method will be used, which is to derive a score based on all the confounding factors previously identified. The probability to be treated with a given therapeutic combination will be estimated using a logistic regression model (with all confounding factors and treatment as dependent variable). Several checks will be performed to ensure a good balance of propensity score and of covariates between apixaban and comparison groups:First, the treatment group propensity score distribution will be analyzed with a graphical representation. If no overlap between distributions is observed, patients will be defined as different, so comparisons would not be performed.Then, the balance of propensity score across treatment and comparison groups will be checked, with comparison of means. The balance of covariates across treatment and comparison groups will be checked using standardized difference.^17^

If no balance, a new propensity score model will be specified (deletion of variables or transforms).^17^

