#### Secondary outcomes

3.4.2

For the secondary outcomes, the comparison between patients initiating apixaban and patients initiating each of the other anticoagulant treatments (dabigatran, rivaroxaban, and VKAs) will be performed only in the four sub‐cohorts of anticoagulant‐naive patients.

For all other descriptive objectives, the analyses will be performed in the eight sub‐cohorts.

Estimation by anticoagulant treatment and for both populations (anticoagulant‐naive and anticoagulant‐experienced patients) as follows:Quantitative variables will be described with the sample size, mean, standard deviation, median, interquartile range, minimum and maximum.Qualitative and ordinal variables will be described with the sample size and frequencies.

Analyses in anticoagulant‐naive and anticoagulant‐experienced populations as follows:The major characteristics of patients will be described for each anticoagulant treatment.Treatment patterns at anticoagulant initiation, over time, and concomitant treatment will be tabulated by anticoagulant treatment.Time‐to‐discontinuation will be estimated and plotted using cumulative incidence function by anticoagulant treatment.Healthcare resources utilization will be described by anticoagulant treatment.

For each endpoint of interest in the study, only the first evidence of its event will be considered in the analyses. Cox models have been chosen to align with the methodology used in other OAC publications. As this study has been conducted to address a specific request from French health authorities, the comparability of the methods with other OAC publication was an important contributor of the analytical choices made a priori.

Cox models or Fine Gray models are planned to be used in the analyses. The final choice of model will be based on the observed death rates, that is, in case of a high likelihood of competing risk of death, Fine Gray models will be used rather than Cox models.

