
Despite the numerous advantages related to the use of the SNIRAM database in pharmacoepidemiology studies, this database has limitations. First, there is a risk of incomplete data collection due to the research method using identification of patients through ICD‐10 diagnosis in the SNIIRAM database. Therefore, an algorithm needs to be applied to catch AF patients and can induce a diagnosis bias. Second, only major bleeding resulting in hospitalization is collected through PMSI. Less severe bleeding, requiring emergency care but no hospitalization will not be identified in the database. Third, due to the claim‐based retrospective nature of our study, treatment discontinuation of VKA could be biased due to the nature of individual variable dosing of VKA. Nevertheless, algorithms were performed to overcome these issues. In addition, as we used INR testing during hospitalization as a proxy for VKA dispensation, we might have miss patients who presented temporary interruption of their anticoagulant treatment. As the HAS requested clinical practice data documenting the therapeutic benefit of apixaban under actual conditions of use, compared with the standard oral anticoagulant treatment recommended in France (vitamin‐K antagonists, dabigatran, and rivaroxaban), only apixaban off‐label use were collected and therefore, off‐label data on other anticoagulants could not be reported. Fourth, one of the main limitations of this database, as is the case for many administrative databases, is the lack of information for certain clinical or biological risk factors for stroke, thromboembolism or bleeding. Without such information it is not possible to compare the distribution of these risk factors between anticoagulant treatments. Adjusting/matching for large numbers of covariates ascertain from patients' healthcare claims data improved control of confounding, as these variables could collectively be proxies for unobserved factors. Finally, future analyses of this study could also include complementary comparative approaches, such as using IPTW, which is another and probably better method to estimate an average treatment effect in the entire population if the treatment might be offered to every member of the population (ATE).

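### The main comparative method, propensity score adjustment, is labelled as estimating the ATE but in general does not, and no planned analysis does so by weighting or standardisation

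*Protocol article*

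**What the plan says.** Section 3.4.1 lists the methods for controlling confounding and attaches an estimand to two of them. The first, labelled ATE, is "adjustment on propensity score (estimation of the average treatment effect in the entire population if the treatment might be offered to every member". The second is "matching on propensity score (estimation of the average treatment effect of matched subjects who ultimately received the treatment, ATT"). Two sensitivity analyses follow: "using high dimensional propensity scores, and adjustment on confounders". The section then ranks them: "The main method will consist in propensity score adjustment to compare groups of patients with the same characteristics". There is one score for each of the three pairwise comparisons (apixaban against dabigatran, rivaroxaban and VKAs), and each "will be estimated using a logistic regression model".

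Section 3.4.2 gives the outcome model: "Cox models or Fine Gray models are planned to be used in the analyses". It also restricts the comparisons to the four anticoagulant-naive sub-cohorts.

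The last paragraph of the Discussion (section 4) says that "future analyses of this study could also include complementary comparative approaches". The example it gives is weighting, put this way: "such as using IPTW, which is another and probably better method to estimate an average treatment effect in the entire population". Neither weighting nor standardisation is among the planned analyses.

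**The concern.** The ATE compares outcomes if every patient in the population received one drug with outcomes if every patient received the other. A Cox or Fine-Gray model with treatment and the score as covariates answers a different question: the relative hazard between patients with the same score. The two can part for two reasons.

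- **Effect heterogeneity.** If the treatment effect varies with the score, the single coefficient is an information-weighted average over scores. It gives little weight to patients whose score is near 0 or 1, whereas the ATE counts every patient equally.
- **Non-collapsibility.** Even when the conditional hazard ratio is constant, it differs from the marginal hazard ratio once events are common and a strong prognostic factor is present.

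The article thus names a population estimand, chooses a main method that does not target it, and says that an unplanned method probably would do better. At stake is how the apixaban comparisons are read. They answer a health-authority request for evidence against standard treatment, and a result labelled as a population effect may be taken as one.

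**Working it through.** The article states no sample size, event rate or effect size for the comparisons, so there is no figure to reproduce. The check is whether score adjustment returns the ATE. **Every input below is an assumption.**

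**1. Rare-event model, one confounder.** X is standard normal. The one-year hazards are h0 = 0.03·exp(pX) untreated and h1 = h0·exp(log 0.80 + gX) treated. The score is logit e = a + sX.

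The true ATE ratio is E[h1]/E[h0] = 0.80·exp(gp + g²/2).
- p = −0.5, g = 0.3: 0.80·exp(−0.15 + 0.045) = 0.720
- p = +0.5, g = 0.3: 0.80·exp(0.15 + 0.045) = 0.972

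The score-adjusted ratio is exp(β) from the population Poisson fit log μ = α + βA + γe.

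| p | g | True ATE | a=−0.5, s=1 (40% treated) | a=−1.2, s=1 (27%) | a=−1.2, s=1.5 (30%) |
|---|---|---|---|---|---|
| −0.5 | 0.3 | 0.720 | 0.790 | 0.834 | 0.859 |
| −0.5 | 0.1 | 0.765 | 0.793 | 0.808 | 0.821 |
| −0.5 | −0.3 | 0.972 | 0.875 | 0.829 | 0.796 |
| +0.5 | 0.3 | 0.972 | 0.962 | 1.021 | 0.994 |
| +0.5 | 0.1 | 0.845 | 0.847 | 0.863 | 0.857 |
| −0.5 | 0 | 0.800 | 0.803 | 0.804 | 0.808 |

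The gaps in the first row are 0.070, 0.114 and 0.139. Changing only the sign of p (fourth row) cuts them to 0.010, 0.049 and 0.022. Reversing the interaction (third row) gives gaps up to 0.972 − 0.796 = 0.176 in the other direction, so the benefit is exaggerated.

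With the logit of the score as covariate, the homogeneous row becomes 0.800 throughout, so that small gap is one of functional form. The first row becomes 0.797, 0.845 and 0.884, so functional form does not explain the gap under heterogeneity.

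**2. Cox simulation.** 1.5 million patients per scenario, one normal confounder, true score, one year of follow-up. The true ATE hazard ratio comes from both potential outcomes. The conditional hazard ratio at X = 0 is 0.7 (0.5 in the third row). Moderate separation is logit e = −0.5 + X; strong is −1.5 + 1.5X.

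| Scenario | Score-adjusted | IPTW | True ATE |
|---|---|---|---|
| Homogeneous, about 2% events | 0.701 | 0.697 | 0.699 |
| Homogeneous, about 9% events | 0.701 | 0.704 | 0.709 |
| Homogeneous, about 33% events, strong prognostic factor | 0.500 | 0.584 | 0.585 |
| Interaction +0.3, about 2% events, moderate separation | 0.836 | 0.835 | 0.833 |
| Interaction −0.3, same | 0.599 | 0.626 | 0.638 |
| Interaction +0.3, about 2% events, strong separation | 0.893 | 0.848 | 0.849 |
| Interaction −0.3, same | 0.548 | 0.628 | 0.642 |

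IPTW stays within 0.014 of the true ATE (0.642 − 0.628). Score adjustment agrees with the ATE in some scenarios and misses it by up to 0.094 (0.642 − 0.548) in others. Adding a squared term, on the logit scale, leaves 0.890 and 0.563 in the last two rows.

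**The case against.** The strongest reply is that the defect lies in a label, and that its size depends on chosen inputs. Much of this stands.

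- **Inputs.** An interaction of 0.3 per SD is large. The ratio runs from 0.80·exp(−0.6) = 0.44 at −2 SD to 0.80·exp(0.6) = 1.46 at +2 SD, with about 23% of patients above 1. No single summary would serve such a population well. With weaker interactions or another sign of the prognostic slope, the gap is often trivial.
- **Undefined term.** The article does not define adjustment or say how the score enters the model. Covariate adjustment is the natural reading, not an explicit statement. The Discussion presents IPTW as an additional approach for later, so weighting is not what is meant.
- **Other analyses and disclosure.** Matching with an ATT target and two sensitivity analyses are planned, and divergence between methods would show. The Discussion discloses the preference for IPTW. But none of these supplies the ATE, and disclosure does not correct the label.

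A reader might infer more than the article supports. One inference is that this undermines the headline result. Section 2 makes estimation of risk by treatment the primary objective; the apixaban comparisons are secondary and confined to anticoagulant-naive patients. Another is that balance cannot be checked when the score is a covariate. It can be checked within score strata or in the planned matched sample, and section 3.4.1 plans overlap plots and standardized differences. A third is that the adjusted hazard ratio is invalid. It remains a legitimate conditional estimate; only the ATE label is unsupported.

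**Conclusion.** The point holds as a mismatch between estimand and method. The main comparative estimate, read as a score-adjusted Cox or Fine-Gray hazard ratio, is conditional on the score and in general is not the ATE that section 3.4.1 assigns to it. The article itself points to a method better suited to the ATE and does not plan it.

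The size cannot be fixed from the document. With rare events and a homogeneous effect it is negligible and the issue is mainly wording. In the rare-event scenarios with a varying effect it is roughly 0.00 to 0.14 on the ratio scale, and up to about 0.18 with the interaction reversed, in either direction. Common events add a separate gap (0.500 against 0.585 in the one such scenario), which could matter for all-cause mortality, also compared, if deaths are frequent. These figures rest on one confounder, a known score and assumed effects, and are not forecasts for this study.

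This should be fixed. Because the comparisons are secondary and the conditional estimate is usable under its proper name, it is not a defect that must block the plan.

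**What to change.** Pre-specify IPTW, or standardisation of the outcome model over the whole comparison population, as the ATE analysis for each of the three pairwise comparisons in anticoagulant-naive patients, using the scores already planned. Use robust variance and report standardized differences in the weighted sample. State any weight truncation or common-support restriction in advance, and say that it narrows the target so that the result no longer refers strictly to the entire population.

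Keep score adjustment as a sensitivity analysis, described as a score-conditional hazard ratio without the ATE label, and keep matching (ATT) beside it. Amend the Discussion so that IPTW is no longer left to future work. At the least, remove the ATE label from score adjustment.

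The cost is plan wording, modest programming and somewhat wider intervals where weights vary. Weighted Cox models keep the comparability with other anticoagulant publications that section 3.4.2 gives as a reason for its choice of model.
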